### Causal Contrast

The estimand of interest in this study, the target causal effect of a sustained lifestyle intervention strategy, is

*E*(*Y*^1,1,1,1^|*C* = 0) – *E*(*Y*^0,0,0,0^|*C* = 0) **(1)**

that is, the expected value of a given health outcome *Y* at the end of follow-up if all participants had increased their adherence to CFG recommendations on healthy food choices and physical activity, when applicable, at all 4 time points (*X_k_=1*, *always intervene*) versus if all participants had maintained their habitual diet and physical activity (*X_k_=0*, *never intervene*). The estimand (equation 1) also indicates that all participants completed the intervention (C=0), that is, in the absence of incomplete follow-up.

The causal contrasts of interest are the observational analogs of intention-to-treat and per-protocol analyses [11]. Given the observational design, participants are not expected to have followed a treatment strategy unknown to them at the time of data collection. Therefore, the primary analysis will be the per-protocol contrast of a sustained lifestyle intervention strategy. In the per-protocol analysis, nonadherence to the hypothetical interventions can be accounted for. In the target trial, participants with a condition after baseline that would have prevented or limited participation in a hypothetical lifestyle intervention would be allowed to discontinue the intervention (eg, lengthy hospitalization, prolonged bed rest, and incident cancer). In the emulation, if such conditions occur in a sufficiently large number of participants, these participants will be “excused” from following the hypothetical intervention [23]. In other words, participants who would have been unable to pursue the study due to major events will not be considered as having incomplete follow-up if they attended the annual assessment. Allowing participants to discontinue adhering to the hypothetical intervention strategy mitigates confounding by the disease burden [23].

The intention-to-treat analysis will be a secondary analysis of a hypothetical point intervention, for example, dietary counseling at baseline only. Notably, it will not be possible to conduct an intention-to-treat analysis identical to that of a controlled study where the interest is to estimate the effect of being *assigned* to an intervention [11]. However, it is possible to conduct an observational analog of the intention-to-treat analysis. In the observational analog, the intention-to-treat analysis aims to estimate the impact of a hypothetical intervention in which adherence is measured at baseline only.

### Statistical Analysis

#### Modeling of Hypothetical interventions

Stratification and multivariable regression (ie, covariate adjustment) are conventional statistical approaches to address confounding in nutritional epidemiology. However, the conventional approaches are not adequate to estimate cumulative treatment effects (eg, diet over time) in the presence of time-varying confounding (eg, weight status over time) and treatment (eg, previous diet) [41,42]. In this study, nonadherence to the hypothetical interventions and incomplete follow-up will be considered using general g-methods for the per-protocol analysis [11,42]. Among g-methods, the parametric g-formula provides the most flexibility for analyses involving hypothetical dietary interventions, as used in previous studies [19,22,43]. Briefly, in the context of an observational study, the parametric g-formula and its implementation into an R package (R Foundation for Statistical Computing) [44] use parametric models to predict the joint history of previous diet and physical activity habits (ie, the hypothetical sustained intervention strategy) and confounding variables. For example, linear regression models are used to predict continuous covariates (eg, body weight), while logistic regressions are used to predict binary or categorical variables (eg, indicator variable for dietary supplement use). The per-protocol causal contrast of the hypothetical intervention presented in Table 2 is then emulated based on Monte Carlo simulated data generated using the g-formula algorithm [44]. The parametric g-formula correctly accounts for time-varying confounding in the presence of feedback between the intervention and the confounding variables, as confounding is addressed using standardization [41,42]. Furthermore, standardization allows for estimating an average causal effect (ie, marginal effect) consistent with the estimand of interest (equation 1) rather than a conditional effect. In summary, “threshold interventions” that depend on the reported dietary intakes or amount of physical activity [43,45] and the parametric g-formula [44,46] will be used to emulate the intervention of *consuming at least x servings of food* and *doing at least x minutes of light to vigorous physical activity.*

Figure 2 presents the causal directed acyclic graph (DAG) of the hypothesized relationship between a sustained lifestyle intervention strategy (*X_0_, X_1_*) and an end of follow-up outcome *Y* for 1 follow-up after baseline (year 1). The model is limited to year 1 for clarity, but the hypothesized causal structure extends to additional follow-ups. The exposure of interest *X_k_* is the joint and cumulative effect of a sustained diet and physical activity intervention strategy measured at baseline and follow-ups.

In the context of this target trial emulation (Figure 2), *P* includes dietary habits before the baseline assessment. *P* can have an effect on baseline dietary habits (eg, previous healthy habits increase the likelihood of baseline healthy habits) and dietary habits throughout the target trial emulation (eg, previous healthy habits increase the likelihood of adhering to healthy habits). Furthermore, *P* influences baseline and time-varying confounding. Finally, given the long-term effect of chronic exposure, *P* potentially affects *Y* directly.

The intention-to-treat analysis is similar to the per-protocol analysis. However, only baseline diet and physical activity habits and covariates are considered, as well as prebaseline diet and physical activity. In both the per-protocol and intention-to-treat analyses, loss to follow-up (eg, nonresponse or missing follow-up and health outcomes not measured) will be accounted for using g-methods such as inverse probability weighting.

**Figure 2 figure2:**
[figure not shown]
Directed acyclic graph depicting the hypothesized relationship among previous dietary exposure, time-varying interventions (diet and physical activity), and covariates. Arrows from the Z node are not shown for clarity but would point toward all baseline and time-varying nodes, as well as the outcome. Only 1 follow-up is shown for visualization purposes, but the hypothesized causal structure extends to additional follow-ups. Subscripts indicate the time points, where 0 represents baseline and 1 represents time point 1.

#### Dietary Assessment

In NuAge, diet during the year before baseline was assessed using 1 semiquantitative food-frequency questionnaire [47]. Dietary intakes at baseline (ie, time point 0) and each annual follow-up (ie, time points 1, 2, and 3) were assessed using 3 repeated face-to-face interviewer-administered 24-hour dietary recalls.

Dietary intakes measured using 24-hour dietary recall are more accurate (ie, have less systematic error or bias) than food-frequency questionnaire [48-50] but are particularly affected by random measurement error (ie, within-individual random error) [50]. When several variables measured with errors are considered simultaneously in a regression model, the regression coefficients may be biased in any direction [51]. To account for random measurement error, the National Cancer Institute Markov Chain Monte Carlo (NCI MCMC) multivariate method could be applied [52]. However, the combination of the parametric g-formula and multivariate measurement error correction using the NCI MCMC method is not feasible. The NCI MCMC method estimates time-invariant measurement error–corrected intakes, while the g-formula algorithm is designed for time-varying exposures.

Recognizing the importance of accounting for measurement error, the correction for measurement error will be reserved for the secondary intention-to-treat analysis. For the intention-to-treat contrast, the time-varying values of exposure and the time-varying values of confounding are not considered. Thus, the NCI MCMC method will be used to obtain measurement error–corrected estimates of the relationship between dietary intakes measured at baseline and outcome at the end of follow-up. Notably, the three 24-hour dietary recalls collected at each time point contribute to reducing random errors, at least to some extent, even in the absence of measurement error correction.

#### Sensitivity Analysis to Assess the Impact of Measurement Error

For the secondary intention-to-treat analysis, results based on the measurement error–corrected and –uncorrected dietary intakes will be compared. The difference between the estimated relationships will allow to extrapolate the impact of not accounting for random errors in the primary *per-protocol* analysis.

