We emphasize that the purpose of emulating a target trial using observational data is to improve the quality of observational analysis [11,14]. In other words, the target trial framework aims to support the coherence between the causal research question and the observational data analysis [26]. However, estimating causal effects with nonexperimental observational data depends on strong assumptions. The key assumptions are that there are no unmeasured confounders, no measurement errors, and no model misspecifications (eg, functional form of covariates and model outcome distribution) [19]. We first recognize that the absence of residual or unmeasured confounding cannot be guaranteed. The extent to which this assumption is sufficiently satisfied depends on the appraisal of covariates considered. In that regard, we have used graphical tools, DAG, to explicitly describe our analytical assumptions and to identify confounding variables [59-61]. Second, the absence of measurement error assumption will not be satisfied considering the use of dietary intake data measured with 24-hour dietary recalls. On one hand, 24-hour dietary recalls have the least systematic error or bias compared with other common instruments, such as food-frequency questionnaires [48,49]. On the other hand, 24-hour dietary recalls are largely affected by within-individual random errors [50], which can cause bias in any direction in multivariable models [51], as in this study. This issue is mitigated, at least to some extent, by using average data from 3 repeated 24-hour dietary recalls at each follow-up. Sensitivity analyses comparing estimates based on measurement error–corrected and –uncorrected baseline dietary intakes will be used to assess the impact of random measurement errors. Third, the absence of model misspecification will be assessed by examining differences between the observed value of time-varying covariates and the predicted value of time-varying covariates as modeled with the g-formula.

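### The baseline-only intention-to-treat comparison cannot show how much random dietary error biases the primary per-protocol estimate, although the protocol says it will

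*Protocol article*

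**What the plan says.** All references are to the protocol article.

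- *Causal Contrast* makes the per-protocol effect of a sustained strategy primary. The estimand intervenes "when applicable, at all 4 time points".
- *Dietary Assessment* says that "the correction for measurement error will be reserved for the secondary intention-to-treat analysis". The reason given is that "The NCI MCMC method estimates time-invariant measurement error–corrected intakes, while the g-formula algorithm is designed for time-varying exposures".
- The same section describes the secondary analysis: "For the intention-to-treat contrast, the time-varying values of exposure and the time-varying values of confounding are not considered". It also warns: "When several variables measured with errors are considered simultaneously in a regression model, the regression coefficients may be biased in any direction".
- *Sensitivity Analysis to Assess the Impact of Measurement Error* then states: "The difference between the estimated relationships will allow to extrapolate the impact of not accounting for random errors in the primary" per-protocol analysis. It attaches no rule, condition or caveat.
- *Principal Findings* concedes that "the absence of measurement error assumption will not be satisfied" and points to the same comparison as the way to judge the impact. Averaging three recalls per visit is the only other mitigation mentioned.

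**The concern.** The reason for not correcting the primary analysis is that the correction method handles one fixed intake per person, while the g-formula needs intakes that change over time. The same mismatch stands in the way of carrying the bias from one analysis to the other. The intention-to-treat analysis has one error-prone measure per food, adjusted for the prebaseline questionnaire. The per-protocol analysis has up to four per food, which partly inform one another, plus confounders that respond to diet.

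The primary outcomes are muscle strength and physical function, and Hypothesis 1 expects no effect of the food guide on muscle health. Attenuation by random error is the obvious rival explanation for a null result there. If the intention-to-treat comparison is offered as the gauge, readers may be told that error matters much more, or somewhat less, than it does for the primary contrast.

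**Working it through.** The protocol states no reliability, attenuation factor or persistence, so there is no figure of its own to reproduce. The question is whether the bias ratio (uncorrected effect divided by true effect) is the same for both contrasts.

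**Assumed inputs (not from the protocol).** One food. Intake X0 to X3 at the four time points, each with variance 1. Prebaseline diet P with variance 1 and correlation 0.5 with X0. Persistence ρ from one year to the next. Outcome effect 0.1 per unit of each X and of P. Measured intake is X plus classical error with variance s = 1/R − 1, where R is the reliability of the recall mean.

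**Baseline contrast, P known exactly.** The variance of X0 given P is 1 − 0.25 = 0.75, so the bias ratio is 0.75/(0.75 + s). At R = 0.6, s = 0.667 and the ratio is 0.75/1.417 = 0.53.

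**Sustained contrast, P known exactly.** Let Σ be the covariance of X0 to X3 given P, with entries ρ^|i−j| − 0.25ρ^(i+j). The effect of a one-unit shift at all four times is the sum of the four coefficients, so the bias ratio is 1ᵀ(Σ + sI)⁻¹Σ1 / 4. At R = 0.6 and ρ = 0.6 this is 0.75.

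**Misstatement factor** = sustained ratio / baseline ratio. Above 1, the intention-to-treat comparison overstates the attenuation in the primary contrast. Here it is 0.751/0.529 = 1.42.

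The calculation was repeated with a questionnaire of reliability 0.5 standing in for P, and the true effect again as benchmark:

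| R | ρ | P exact: baseline, sustained, factor | Questionnaire with error: baseline, sustained, factor |
|---|---|---|---|
| 0.5 | 0.8 | 0.43, 0.72, 1.67 | 0.51, 0.79, 1.54 |
| 0.6 | 0.6 | 0.53, 0.75, 1.42 | 0.64, 0.82, 1.27 |
| 0.75 | 0.4 | 0.69, 0.82, 1.19 | 0.85, 0.89, 1.04 |
| 0.9 | 0.2 | 0.87, 0.92, 1.05 | 1.09, 0.98, 0.90 |

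Over R from 0.5 to 0.9 and ρ from 0.2 to 0.8 the factor runs from 0.90 to 1.67. Values below 1 arise only where questionnaire error leaves residual confounding by earlier diet.

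**With a time-varying confounder.** A separate simulation (300,000 persons per scenario, 27 scenarios) used four time points, a confounder that could respond to diet, an error-prone questionnaire and a linear g-formula. The benchmark was the same analysis with error-free intakes.

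| R | Intention-to-treat ratio | Per-protocol ratio |
|---|---|---|
| 0.4 | 0.28–0.39 | 0.44–0.62 |
| 0.6 | 0.46–0.59 | 0.64–0.78 |
| 0.8 | 0.69–0.79 | 0.82–0.90 |

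The two ratios differed in every scenario. The factor ran from 0.82/0.79 = 1.04 to 0.57/0.28 = 2.0, the latter at R = 0.4, below the range used above. Both ratios stayed between 0 and 1 throughout, so with one food the direction carried over and the size did not.

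**Two foods.** Take two unrelated foods that both follow the first model with P exact, with ρ = 0.6, reliabilities 0.5 and 0.7, and effects +0.1 and −0.075. The true joint effect per time point is 0.025.

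- Baseline: (0.1 × 0.429 − 0.075 × 0.636)/0.025 = −0.19.
- Sustained: (0.1 × 0.669 − 0.075 × 0.823)/0.025 = +0.21.

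Here error reverses the baseline effect but only shrinks the sustained one. The example was chosen, with effects that nearly cancel, so it shows that the direction can fail to carry over, not how often. Table 2 intervenes on six recommended food categories at once.

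**The case against.** A reader might infer that the plan will apply a wrong correction to the primary estimate. The protocol does not support that. Correction is confined to the intention-to-treat analysis, no factor or rescaling rule is given, and *Principal Findings* describes the purpose only as assessing impact. The factors above measure how far the bias would be misjudged, not an error in a planned estimate.

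The protocol is also candid. It says the correction cannot be combined with the g-formula, that bias may go in any direction, that the no-error assumption fails and that random error is a limitation. A qualitative indication is a possible reading of the comparison. These caveats concede bias in the primary result, but none limits the claim that the intention-to-treat difference lets its impact be extrapolated.

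The size rests on assumed values and simple linear models, with a uniform shift in place of threshold interventions. With high reliability and low persistence the gap is small (0.79 against 0.82 in one scenario). That stands, and it is why no single percentage should be quoted. It does not rescue the inference, because nothing in the protocol shows that the study lies in that corner.

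Finally, an error analysis inside the g-formula is heavy: several outcomes, four strategies, sex strata and at least 200 bootstrap replicates. That is a fair reason to limit its scope, not to keep the sentence.

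**Conclusion.** The concern holds in this form: the intention-to-treat comparison does not in general give the size of the random-error bias in the per-protocol estimate, and the protocol says without condition that it will. Under the stated one-food assumptions the misstatement is a factor of about 0.9 to 1.7, usually an overstatement of attenuation. It grows with lower recall reliability and stronger persistence. With several error-prone foods a different direction is possible, but it is not shown to be likely. The primary estimate itself is unaffected; what would be wrong is the account given of its bias. No measurement-error analysis that acts on the primary contrast is described.

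**What to change.** 1. Delete the extrapolation sentence in *Sensitivity Analysis to Assess the Impact of Measurement Error*. Present the corrected and uncorrected intention-to-treat results as a qualitative, baseline-only indication, and align the matching sentence in *Principal Findings*.
2. Add a sensitivity analysis on the per-protocol contrast. Estimate within-person variance from the repeat recalls, then either run simulation-extrapolation within the g-formula for the main primary outcomes, or a bias analysis over a stated range of reliability. Report the result next to the uncorrected estimate.
3. State the error model in advance. Intakes are non-negative and correlated, total food and total beverage intake carry the same recall error, and *Eligibility Criteria* requires only one baseline recall, so some participants may not have three.

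No new data are needed. The costs are extra g-formula runs, wider intervals on the extrapolated estimate, and dependence on the extrapolation function and error model. Restricting the analysis to the main primary outcomes in the whole sample keeps the computing manageable.

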#### Physical Activity Assessment

Physical activity throughout the study will be assessed using the Physical Activity Scale for the Elderly questionnaire [53,54]. Rather than the total Physical Activity Scale for the Elderly score, specific questions estimating the total time of physical activities will be used to be consistent with the intervention strategy.

#### Covariates and Subgroups

To the extent permitted by the number of observations for each outcome, continuous covariates will be modeled using restricted cubic splines with 3 to 5 knots (at percentiles 10-50-90, 5-35-65-95, or 5-27.5-50-77.5-95) [55]. Categorical covariates will be modeled to ensure a sufficient sample size at each level.

The effect of dietary changes will be estimated for the entire sample. The sample will also be stratified by biological sex to reflect both potential biological differences and, to some extent, gender differences (although not reported).

#### Variance Estimation

The variance will be estimated using a minimum of 200 bootstrap sample replicates to consider uncertainty at each step of the estimation [56].

#### Software and Code

The main statistical analyses will be conducted using R software (version 4.3.1 or greater) and the *gfoRmula* package [44,57]. The manuscript results will be generated using Quarto markdown (Posit PBC). Codes for main analyses and generation of manuscript results will be shared in a publicly available code repository.

### Ethical Considerations

The original NuAge protocol was approved by the research ethics boards of the *Institut universitaire de gériatrie de Montréal* and the *Institut universitaire de gériatrie de Sherbrooke* (Quebec, Canada). The NuAge Database and Biobank [58] has received approval by the *Centre intégré universitaire de santé et de services sociaux de l’Estrie—Centre hospitalier universitaire de Sherbrooke* Research Ethics Board. Secondary analyses of data from the NuAge Database and Biobank for the study described in this protocol are approved by the McGill University Research Ethics Board Office (#22-11-041).

All participants of NuAge provided informed consent. From the initial cohort of 1793 participants, 1753 (97.77%) agreed to the integration of their data and biological samples into the NuAge Database and Biobank for future studies.

Secondary analyses based on the NuAge Database and Biobank use deidentified data, which do not allow participants to be identified by the investigators.

NuAge participants voluntarily consented to participate and were not provided with monetary compensation.

## Results

Data collection for NuAge was completed in June 2008. For this study, the main analysis based on the final curated data started in May 2024. The manuscript will be written according to the Strengthening the Reporting of Observational Studies in Epidemiology statement. We anticipate the submission of the manuscript to a peer-reviewed academic journal by February 2025.

## Discussion

### Principal Findings

In this study protocol, we have described a target trial to assess the effect of adhering to CFG recommendations on healthy food choices. The emulation will be performed using data from the NuAge Database and Biobank [58]. Benefiting from the flexibility of observational data, we also aim to compare adherence to multiple reformulations of CFG recommendations, including the effect of increasing the intake of protein-rich foods and the amount of aerobic physical activity on selected health outcomes. Furthermore, we have outlined the rationale for using simulated diets to emulate adherence to CFG recommendations, the process of selecting covariates to attempt to emulate randomization with causal diagrams, and the challenges of addressing random measurement error.

We emphasize that the purpose of emulating a target trial using observational data is to improve the quality of observational analysis [11,14]. In other words, the target trial framework aims to support the coherence between the causal research question and the observational data analysis [26]. However, estimating causal effects with nonexperimental observational data depends on strong assumptions. The key assumptions are that there are no unmeasured confounders, no measurement errors, and no model misspecifications (eg, functional form of covariates and model outcome distribution) [19]. We first recognize that the absence of residual or unmeasured confounding cannot be guaranteed. The extent to which this assumption is sufficiently satisfied depends on the appraisal of covariates considered. In that regard, we have used graphical tools, DAG, to explicitly describe our analytical assumptions and to identify confounding variables [59-61]. Second, the absence of measurement error assumption will not be satisfied considering the use of dietary intake data measured with 24-hour dietary recalls. On one hand, 24-hour dietary recalls have the least systematic error or bias compared with other common instruments, such as food-frequency questionnaires [48,49]. On the other hand, 24-hour dietary recalls are largely affected by within-individual random errors [50], which can cause bias in any direction in multivariable models [51], as in this study. This issue is mitigated, at least to some extent, by using average data from 3 repeated 24-hour dietary recalls at each follow-up. Sensitivity analyses comparing estimates based on measurement error–corrected and –uncorrected baseline dietary intakes will be used to assess the impact of random measurement errors. Third, the absence of model misspecification will be assessed by examining differences between the observed value of time-varying covariates and the predicted value of time-varying covariates as modeled with the g-formula.

